### Cancer survivorship care

The nature and incidence of late effects underscore the need for high-quality long-term follow-up care for cancer survivors. Therefore, the Centre of Expertise for Cancer Survivorship in the Netherlands developed the innovative Personalized Cancer Survivorship Care model with three important purposes: (1) to earlier detect and (2) treat late effects or (3) to preserve survivor’s health [20]. Care within this model is delivered according to the principles of person-centred care (PCC) as developed by Ekman et al. [21]. Partnership between the patient and the medical professional is the most important feature in PCC. This partnership, based on an equal footing, gives the patient an active role in his or her own care. Hence, PCC is thought to be an important contributing factor in promoting self-efficacy and self-management. Stimulating self-efficacy and self-management helps patients to take control of their own lives and to obtain a higher quality of life [22]. This illustrates the necessity of incorporating PCC in cancer survivorship care.

### eHealth interventions

Given limited healthcare resources, provision of follow-up care needs to be both sustainable and cost-effective [23]. Electronic health (eHealth) interventions are accessible to cancer survivors from a home situation, making eHealth an attractive means to deliver interventions with limited resources [24]. In addition to the cost-effectiveness promises of eHealth interventions, they can also be favourable for survivors as they are released from unnecessary clinic visits that may hinder the survivors’ daily life activities [25]. Post and Flanagan report in their integrative review potential for web-based survivorship interventions to be feasible and acceptable in breast cancer survivors [25]. In addition, a study of Abrahams et al. found Internet-based cognitive behavioural therapy to be accessible and effective in reducing severe fatigue and related symptoms in breast cancer survivors as well [26].

### REVIVER interventions

In order to treat survivors for late effects of cancer treatment in a cost-effective way with limited burden, an eHealth solution for survivors of childhood, adolescent and young adult (CAYA) cancer was developed and has recently been implemented at the Centre of Expertise for Cancer Survivorship. These so-called REVIVER interventions, with PCC as core principle, are part of cancer survivorship care to improve the following direct or indirect late effects of cancer treatment: CRF, self-efficacy and self-management or lifestyle. The interventions are led by a trained nurse who applies either cognitive behaviour therapy (CBT), motivational interviewing (MI) or a combination of both to help survivors overcome their late effects. However, there is a need for feasibility and potential effectiveness evaluations in order to implement the REVIVER interventions on a wider scale.

Our primary study objective relates to the assessment of the feasibility of the REVIVER interventions and can be broken down into two specific objectives:
Determine feasibility of the REVIVER interventions for CAYA cancer survivors, in terms of:
DemandAdherence to the sessionsAcceptability (e.g. content and delivery)Practicality (e.g. mode of delivery)Integration/implementation (e.g. facilitators and barriers)
2.Determine feasibility of the REVIVER interventions for the medical professionals, in terms of:
Acceptability (e.g. content, delivery and referral to interventions)Practicality (e.g. mode of delivery)Integration/implementation (e.g. facilitators and barriers)

Our secondary objective is to gain insight into the potential effectiveness of the REVIVER interventions in CAYA cancer survivors, in terms of quality of life, fatigue, self-efficacy, self-management and lifestyle.

## Methods

The protocol of the REVIVER study is drafted according to the COREQ checklist and STROBE Statement [27, 28].

### Design

The REVIVER study will involve a mixed methods research approach. Feasibility will primarily be assessed with qualitative measures, i.e. semi-structured interviews. Quantitative measures will be used to determine adherence to and gain insight into the potential effectiveness of the REVIVER interventions. Therefore, we will apply a single arm pre- and post-test design, with three different measurement points: baseline (T0), following the last session (T1) and 6 months post-intervention (T2). Figure 1 outlines the stages of participation in the REVIVER study interventions.

**Fig. 1 Fig1:**
[figure not shown]
Flowchart REVIVER study

### Study population

#### CAYA cancer survivors

Our primary study population involves CAYA cancer survivors who are at least 5 years post diagnosis. They are eligible for the REVIVER study if they (i) are referred to one of the REVIVER interventions (see Table 1); (ii) are in complete remission of cancer; (iii) are 16–44 years old at enrolment; (iv) are having a basic proficiency in the Dutch language; (v) are having access to a device with Internet options (i.e. smartphone or tablet); and (vi) have given informed consent. We will exclude cancer survivors (i) whose symptoms of fatigue may be caused by an underlying medical condition as these patients need different treatment (CRF intervention); (ii) suffering from complex endocrine disorders explaining overweight (lifestyle intervention); (iii) suffering from serious cognitive or psychological problems; and/or (iv) participating in an intervention study or other interventions aiming at improving CRF, low self-efficacy, self-management or lifestyle.

**Table 1 Tab1:** Criteria for referral to the nurse-led video-coaching interventions (REVIVER)

For referral to the nurse-led video-coaching interventions, participants must:	
• Be a survivor of childhood, adolescent or young-adult cancer (diagnosed with any type of cancer under the age of 39)	
• Completed treatment with chemotherapy and/or radiation therapy for CAYA cancer (with or without surgery, with or without haematopoietic stem cell transplantation) and/ or treatment for a brain tumour at least 5 years ago	
• Visited the Centre of Expertise of Cancer survivorship outpatient clinic at least once	
• Received one of the following indications:	
o Indication of moderate to severe symptoms of cancer-related fatigue. This can be defined in two ways:	
1. Fatigue score ≥ 18 assessed by the Short Fatigue Questionnaire [29]	
2. Fatigue interfering with daily life activities and fatigue lasting at least 6 months	
o Indication of need for more empowerment. This can be defined in two ways:	
1. General Self-Efficacy Scale score ≤ 29 [30]	
2. Late effect doctor of the Centre of Expertise for Cancer Survivorship indicates a low empowerment state of the survivor after anamnesis during consultation at the outpatient clinic	
o Indication of present unhealthy lifestyle factors given by late effect doctor of the Centre of Expertise for Cancer Survivorship outpatient clinic after anamnesis. Unhealthy lifestyle factors include:	
1. A BMI of ≥ 25	
2. Smoking	
3. A low physical activity level	

#### Medical professionals

The second study population is consisting of medical professionals affiliated with the Centre of Expertise for Cancer Survivorship Care and involved with the REVIVER interventions. This sample includes nurses and doctors with late effect expertise and members of the psychosocial expert team.

### Sample size

#### Feasibility evaluation

For feasibility evaluation with semi-structured qualitative interviews, we will recruit a small group of CAYA survivors from the survivors participating in the REVIVER study for potential effectiveness evaluation by means of purposive sampling. The exact number of participating CAYA survivors is dependent on data saturation, which is expected to occur after interviewing approximately 15 CAYA survivors. In addition, all medical professionals (N = 9) involved in CAYA survivorship care at the Centre of Expertise for Cancer Survivorship Care will be recruited for qualitative interviews, including late effect nurses (N = 2) and doctors (N = 4), respectively, and members of the psychosocial expert team (N = 3).

#### Potential effectiveness evaluation

The REVIVER study was primarily designed for feasibility evaluation of the REVIVER interventions. Our secondary aim is to gain insight into the potential effectiveness of the interventions. We estimate that a total of 60 CAYA cancer survivors with 20 survivors per type of intervention is feasible to reach this aim.

This sample size is realistic considering the number of CAYA survivors invited to the outpatient clinic at the Centre of Expertise for Cancer Survivorship per month (± 48) and the study running time of 24 months. Approximately 1 out of 10 CAYA survivors will be eligible for the interventions and be referred to the REVIVER interventions, resulting in a total of 116 eligible survivors after 24 months. Assuming a recruitment rate of 50%, a sample size of 60 will allow us to gain sufficient insight into potential effectiveness of the REVIVER interventions.

### REVIVER interventions

The REVIVER interventions are designed for CAYA survivors to receive coaching to cope with direct or indirect late effects of cancer and are delivered by qualified nurses via secured screen-to-screen video calling software. The interventions, elaborating on PCC principles, are aimed at improvement of (i) symptoms of CRF, (ii) self-efficacy and self-management or (iii) lifestyle. The REVIVER interventions consist of an intake, 3 to 6 screen-to-screen video-coaching sessions and a reflection session. On average, the intake session as well as the coaching sessions will be delivered within a 3-month time period. After a 6-month period in which the survivor can actively work on his or her goals set during the coaching sessions, a reflection session will follow. Depending on the type of intervention, the content is based on CBT and/or MI techniques (Table 2). Fidelity of the REVIVER interventions will be pursued in the three following ways:

**Table 2 Tab2:** REVIVER interventions

Goal	To empower, to motivate and to coach CAYA survivors to actively work on improving and managing either CRF, self-efficacy and self-management or lifestyle
Type	Individual eHealth nurse-led video-coaching interventions delivered during screen-to-screen sessions
Duration	An intake session, 3–6 coaching sessions over a time course of approximately 3 months, and a 6-month follow-up reflection session. Average duration of each session is 30–45 min
Basic principle	Person-centred care
Structure	
• Phase 1 (intake) *Engaging with survivor/focus setting*	During the intake, the nurse will reflectively listen to the survivor’s narrative, try to build a mutually trust with the survivor and explore the survivor’s stage of change. Focus for the following sessions will be discussed
• Phase 2 (3–6 sessions) *Coaching with evidence-based modules of CBT and/or MI*	According to needs and preferences of the survivor, 3–6 coaching sessions will follow Content of the interventions: o *CRF*: module of cognitive behaviour therapy light for chronic fatigue after cancer [31] o *Empowerment*: module cognitive behaviour therapy on four-phase recovery for cancer survivors and motivational interviewing for goal setting [32] o *Lifestyle*: motivational interviewing according to the stage of change of survivor [33]
o Phase 3 (reflection session) *Reflection on last period, sustainable goal setting*	During the reflection session, the survivor’s progress will be reviewed, and if needed, new strategies will be made to still achieve the goals made earlier. In addition, plans will be made to make it a sustainable goal

#### 1.Competence of nurses

The nurses are qualified to deliver the REVIVER interventions based on CBT and/or MI techniques by following a training on CBT and a certified course on MI techniques. In addition, to evaluate the CBT coaching sessions, the nurses have regular (approximately once every 2 months) peer-to-peer coaching with a medical psychologist with experience on CBT.

#### 2.Self-reported adherence of nurses to intervention protocol

Following every intake, coaching or reflection session, the nurses are instructed to fill out an online checklist to check for adherence to the intervention protocol. The checklist includes questions on, for example, the survivor’s story (i.e. stage of change) and facilitators and barriers perceived by the nurses.

#### 3. Adherence of nurses to intervention protocol according to survivors

Following the last coaching sessions, a number of survivors are asked to participate in an interview on facilitators and barriers of the interventions. In this interview, survivors are also asked on the important components of the intervention protocol to check adherence of the nurses to the protocol.

### Study procedures

CAYA cancer survivors will be mainly recruited by late effect doctors affiliated with the Centre of Expertise for Cancer Survivorship while attending a regular medical follow-up consultation at the outpatient clinic. During consultation, when applicable, the REVIVER interventions will be introduced and discussed by the doctor.

Another flow of survivors is coming from the psychosocial expert team of the Centre of Expertise for Cancer Survivorship Care. The medical psychologists or occupational physician may decide, after treatment and/or consultations, to refer the CAYA survivor to the interventions as well. The decision to refer the survivor to the interventions will always be based on shared decision-making. After referral to the interventions, the nurses of the REVIVER interventions will inform the survivor on the REVIVER study and ask consent to participate in the study.

All questionnaire assessments for each measurement moment (T0, T1 and T2) and intervention type are listed in Table 3.

**Table 3 Tab3:** Schedule with specific measurements for survivors for each measurement moment

	Average min to complete	REVIVER interventions		
		T0	T1	T2
*Questionnaires*				
• Standard anamnesis questionnaire	20	X		
• Health-related quality of life (QLQ-C30) [34]	5–10	X	X	X
• Fatigue (CIS20r) [35]	5–10	X	X	X
• Self-efficacy (General Self-Efficacy Scale) [30]	5–10	X	X	X
• Self-management (SeMaS scale) [36]	5–10	X	X	X
• Lifestyle (Leefstijlvragenlijst) [37–40]	15–20	X	X	X
• Physical activity (SQUASH questionnaire) [41]	3–5	X	X	X
*Interviews*				
• Interview experiences REVIVER interventions^*^	45–60		X	

^***^Only applicable to a small sample (N = 10–15) of survivors participating in the evaluation part of the REVIVER study

#### Feasibility evaluation

The survivors for feasibility evaluation will be recruited from the sample of survivors of the potential effectiveness evaluation part of the REVIVER study. During the last video calling session of the REVIVER intervention, the nurse will approach survivors to ask consent to participate in an interview and to be audio recorded. The interviews will take place in the weeks following the last session of the intervention. Beforehand, the researcher will explain the goals for doing this research. Average duration of each interview will be approximately 45–60 min.

Likewise, at the end of the study period, interviews with an average duration of 30–45 min will be conducted with the medical professionals by the same researcher with the medical professional’s consent for audio to be recorded.

An interview guide for the survivors will be developed by the researchers to (semi)structure the interviews (available on request). The guide will contain questions on mode of delivery, content and delivery and facilitators and barriers of the interventions. It will conclude with the survivors’ intentions to continue using the learned strategies to cope with symptoms of fatigue and low self-efficacy level or to adopt/maintain a healthy lifestyle in daily life. For medical professionals, the focus of the guide will be on the practicality of the interventions, fit within the organizational culture and perceived facilitators and barriers. The interview guide will be tested as a pilot in CAYA cancer survivors and other medical professionals affiliated with the Centre of Expertise for Cancer Survivorship. The survivors and medical professionals will be interviewed by an independent researcher who is not involved with the interventions. Both the survivors and medical professionals will be provided with a summary of the results following the end of the study. The nurses’ reports, written after each session with the survivor, will be analysed to assess adherence to the interventions.

These reports contain information on duration and frequency of the sessions, type of module/phase of MI, goals set and goals completed by the survivor. In addition, data on perceived facilitators and barriers of the REVIVER intervention will be collected from the reports as well.

#### Potential effectiveness evaluation

To gain insight into the potential effectiveness of the REVIVER interventions, data from different sources will be extracted. First, we will collect socio-demographic and clinical information from the medical records. Secondly, to assess information on the amount and duration of the sessions needed per survivor, data from the nurses’ reports will be extracted.

Lastly, the survivors are provided with questionnaires at three different time points; prior to the sessions at baseline (T0), immediately following the last session (T1) and at 6 months follow-up (T2). As part of care as usual at the Centre of Expertise for Cancer Survivorship, the General Self-Efficacy (GSE) Scale is incorporated in the standard anamnesis questionnaire that is provided to every survivor attending the outpatient clinic. Therefore, a baseline measurement of self-efficacy can be derived from the anamnesis questionnaire which is incorporated in the survivor’s medical record.

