#### Potential effectiveness evaluation

All analyses will be conducted with the statistical software program SPSS (v25). Descriptive analyses will be conducted using mean with standard deviation, median with interquartile range and frequency for baseline characteristics. These variables include gender, age at intervention and treatment, socio-economic status, previous cancer diagnosis and treatment received. The validated questionnaires will be scored and analysed according to the instructions given by the authors of the questionnaires [49]. Potential covariates such as duration and amount of sessions per survivor will be presented as mean and standard deviation as well. To examine differences in the outcome measures over time, a mixed effect model with random intercept and slope will be used. In total, two nurses are assigned to deliver the interventions. The nurse who delivers the interventions may influence the survivor’s outcome. Therefore, nurse is here considered as a random effect. The outcome measures will serve as independent variables in this model with time and potential covariates as dependent variables. Tukey’s HSD test will be used as well to adjust for multiple comparisons. Due to limited power of our study, we will report data with 95% confidence intervals where needed. In addition, all data of our hypothesis testing will be treated as preliminary and with caution. Lastly, we will analyse all data according to the intention-to-treat analyses.

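### T1 and T2 hang on the last of a variable number of sessions, so survivors who stop attending have no workable assessment date in a promised intention-to-treat analysis

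*Protocol article*

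**What the plan says.** All references are to the protocol article, Methods.

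- **Assessment times.** The Design section sets the three measurements at "baseline (T0), following the last session (T1) and 6 months post-intervention (T2". Study procedures, Potential effectiveness evaluation, repeats the rule: "immediately following the last session (T1) and at 6 months follow-up (T2". Both anchor T1 to an event. T2 is counted from the end of the intervention and so inherits that anchor.
- **Number of sessions.** Table 2, Phase 2: "According to needs and preferences of the survivor, 3–6 coaching sessions will follow". Study procedures likewise treats the count as driven by need, recording "the amount and duration of the sessions needed per survivor".
- **Length of coaching.** REVIVER interventions section: "On average, the intake session as well as the coaching sessions will be delivered within a 3-month time period". This is an average; no window or maximum is stated.
- **Reflection session.** Same section: "After a 6-month period in which the survivor can actively work on his or her goals set during the coaching sessions, a reflection session will" take place. It is also part of the intervention.
- **Attendance.** Outcome measures, Feasibility evaluation, scores adherence as the share of planned sessions attended, so incomplete attendance is anticipated.
- **Analysis.** Analyses, Potential effectiveness evaluation: "a mixed effect model with random intercept and slope will be used", and "Lastly, we will analyse all data according to the intention-to-treat analyses". The number and duration of sessions are named as potential covariates.

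**The concern.** An intention-to-treat analysis needs outcome assessments that fall due whether or not the participant attends. Here the trigger for T1 is attendance itself. When someone drifts away, nobody knows at the time that the session just held was the last, so nothing prompts T1 and there is no end of intervention from which to count six months to T2. Staff would have to improvise, or the assessments would be missed.

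The second worry is that the trigger may be related to the outcome. If a survivor's current state influences when coaching ends, T1 is taken at a selected moment, and ordinary fluctuation in fatigue, self-efficacy or quality of life can appear as change.

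The study has no control group in which the same timing rule could offset this. The Discussion section puts the three measurement points forward in place of a control group, and the Abstract makes a later randomised trial conditional on feasibility and potential effectiveness.

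**Working it through.** **1. Following the rule for different survivors** (months from intake, using the article's average coaching length)

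| Survivor | T1 | T2 |
|---|---|---|
| Finishes coaching, average pace | about 3 | 3 + 6 = about 9 |
| Finishes faster or slower | earlier or later, no limit stated | T1 + 6 |
| Stops attending before the planned end | no trigger | nothing to count from |

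This takes the last session to be the last coaching session. If it meant the reflection session, T1 would fall at about 9 months and T2 at about 15. The wording should exclude one reading.

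**2. What losing early stoppers could do** (illustration; every input is assumed except the sample size of 60)

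Let q be the share without T1. Completers gain 0.30 SD and early stoppers change by d. The change in all participants is (1 − q) × 0.30 + q × d; the analysis of those measured shows 0.30 throughout.

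| q | Measured, of 60 | d = 0 | d = −0.2 |
|---|---|---|---|
| 10% | 54 | 0.27 | 0.25 |
| 20% | 48 | 0.24 | 0.20 |
| 30% | 42 | 0.21 | 0.15 |

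**3. What state-dependent timing could do at T1**

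The article gives no stopping rule and no variance components, so all of these are assumptions: no true effect; total SD 1; within-person fluctuation 20%, 30% or 40% of variance; session-to-session correlation 0, 0.5 or 0.8 (first-order autoregressive); optional stop after session 3, 4 or 5, otherwise session 6; T1 taken at the stop; 400,000 simulated survivors per setting. The state at the stopping decision is compared either with the survivor's usual level or with T0.

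| Assumed rule | Mean T0–T1 change |
|---|---|
| Stop when better | +0.05 to +0.44 SD |
| Stop when worse | −0.05 to −0.44 SD |
| Session number unrelated to state | 0.00 SD |
| T1 at one fixed session for everyone | 0.00 SD |

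The upper end can be checked by hand. With correlation 0 and the usual-level rule, a survivor stops at session 3, 4 or 5 with probability 1 − (1/2)³ = 7/8, with mean state √(2/π) = 0.798 within-person SD. Those reaching session 6 average 0. At a 40% within-person share the gain is 7/8 × 0.798 × √0.40 = 0.44 SD.

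**4. T2**

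Placing T2 nine session intervals after T1 (an assumption standing in for six months), the mean T0–T2 change in the same simulations is at most about 0.02 SD in either direction. The fluctuation has largely died out by then.

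**5. Whether the planned analysis repairs it**

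Session number is measured after baseline and may itself be driven by the outcome, so using it as a covariate does not undo outcome-dependent timing. The mixed model can use incomplete records, but a survivor with T0 only says little about change, and the result then rests on the missing values being predictable from what was observed.

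**The case against.** **No stopping criterion is stated.** A reader might infer that survivors are measured when they feel well enough to stop, and that T1 is therefore biased towards improvement. The article does not say so. The number of sessions could be agreed early; scoring adherence against planned sessions suggests a plan exists. Preferences could equally mean stopping for lack of benefit, and reversing the assumed rule reverses the sign. Nor do those who continue to session 6 add a spurious gain: under the stop-when-better rules their mean T1 state is at or below their usual level. This objection stands.

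**T1 is not named as the main signal.** Quality of life is assessed at three time points and modelled over time, and the artefact is negligible at T2. This also stands.

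**Dates for non-attenders are detail for the full protocol.** This stands only in part. The article does more than leave a window open: it states the trigger, twice, and that trigger fails for early stoppers, whom the promised analysis has to include.

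**An end-of-intervention reading is deliberate.** The Abstract asks for one, and three months is only an average. Moving T1 to three months for everyone would mix finished and unfinished survivors and alter what is estimated. This is fair, and the fix allows for it.

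**Effectiveness is secondary and labelled preliminary.** True, and it lowers the severity. Caution in interpretation does not, however, supply the missing assessments.

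**Conclusion.** The point holds as a minor one. The firm part needs no assumption about behaviour: T1 depends on the last session, T2 depends on T1's anchor, and a survivor who stops attending has no workable date for either, although all data are to be analysed by intention to treat. How much this matters depends on how many stop and how they fare, which the article does not give; the drop-out figures above only illustrate it.

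The timing effect at T1 is a possibility of unknown sign and size: zero if session number is unrelated to state, about 0.05 to 0.44 SD in either direction under the assumed rules, and negligible at T2. The documents do not support a claim that the design favours a finding of improvement through the timing of T1.

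**What to change.** - Give T1 and T2 a due date with a stated window, counted from T0 or intake, for every enrolled survivor regardless of attendance.
- Keep T1 as the end-of-coaching reading for those who finish, but send it to everyone, early stoppers included, by a set latest date.
- Place T2 at a fixed time from T0, for example about 9 months (the 3-month average plus 6).
- State whether the last session means the last coaching session or the reflection session, and align the Design, REVIVER interventions and Study procedures sections.
- Record actual assessment dates and use elapsed time in the mixed model. Report the number of sessions completed descriptively rather than as an ordinary baseline covariate.

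**Cost.** The same questionnaires, sent by date as well as by event, plus some tracking of non-attenders. Care and the sample size of 60 are unchanged. The downside is that some survivors may still be in coaching at the T1 due date. The article gives no distribution of coaching length, so their number cannot be estimated from it.

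### The protocol lets the T0 self-efficacy score come from the routine clinic GSE that can also trigger referral, so part of any pre-post rise may be regression to the mean

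*Protocol article*

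**What the plan says.** Four places in the protocol article bear on the self-efficacy baseline.

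- **Study procedures, Potential effectiveness evaluation.** The GSE is, as care as usual, "incorporated in the standard anamnesis questionnaire that is provided to every survivor attending the outpatient clinic". The next sentence draws the consequence that "a baseline measurement of self-efficacy can be derived from the anamnesis questionnaire", which is kept in the medical record. No maximum interval between that form and the first session is given.
- **Table 1, referral criteria.** The empowerment indication can be met in two ways. One is "General Self-Efficacy Scale score ≤ 29". The other has no cut-off: the late effect doctor "indicates a low empowerment state of the survivor after anamnesis during consultation at the outpatient clinic".
- **Study procedures, opening text.** Consent comes after referral: "After referral to the interventions, the nurses of the REVIVER interventions will inform the survivor on the REVIVER study" and ask for consent. A second stream comes from the psychosocial expert team, whose members "may decide, after treatment and/or consultations, to refer the CAYA survivor to the interventions as well".
- **Table 3.** The standard anamnesis questionnaire (20 minutes) is marked at T0. The GSE has its own row (5–10 minutes), marked at T0, T1 and T2. The table does not say whether the T0 entry is a new administration or the value already inside the anamnesis form.

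**The concern.** The anamnesis GSE is the only GSE before referral that the protocol describes. If a survivor is referred because that score is low, and the same score is then used as T0, the baseline is low partly through measurement error and short-term fluctuation. A later score is expected to be higher even if the coaching does nothing. A controlled trial would show the same drift in both arms and cancel it. This study has one arm, and the Analyses section models change over time, so the drift goes into the estimated effect.

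A second issue concerns timing. For a survivor who completes the anamnesis form, then receives psychosocial treatment, and is only then referred, a baseline taken from the form counts any gain from that treatment as a REVIVER gain.

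Self-efficacy is the direct target of one of the three interventions. According to the abstract, signs of potential effectiveness are part of the condition for going on to a randomised trial. The bias runs in the favourable direction, and it cannot be repaired afterwards if no fresh baseline was collected.

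**Working it through.** The protocol gives no figure for this point, so there is none to reproduce. The size below is illustrative.

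**Inputs**
- Mean GSE μ = 30.63: protocol, Self-efficacy section. This is a figure for German cancer patients, not for this clinic.
- Selection at c = 29: Table 1.
- 20 survivors per intervention, 60 in total: Sample size section.
- SD of GSE 4 to 6, and correlation r between two administrations 0.60 to 0.85: assumed, not in the protocol. The Cronbach alpha of 0.85 that it quotes is internal consistency, not retest correlation.
- True intervention effect: zero.

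**Formula.** For normally distributed scores selected at or below c, let a = (c − μ)/SD and λ = φ(a)/Φ(a). The mean of the selecting score is μ − SD·λ. The expected change at the next measurement is (1 − r)·SD·λ.

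**Worked case, SD 5.** a = (29 − 30.63)/5 = −0.326. λ = 0.3783/0.3722 = 1.016. SD·λ = 5.08, so the selected mean is 30.63 − 5.08 = 25.55. The expected rise is 0.40 × 5.08 = 2.03 at r = 0.60, 0.30 × 5.08 = 1.52 at r = 0.70, and 0.15 × 5.08 = 0.76 at r = 0.85.

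**Range, all survivors selected on score**

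| SD | a | SD·λ | Selected mean | Rise, r = 0.60 | Rise, r = 0.85 |
|---|---|---|---|---|---|
| 4 | −0.408 | 4.30 | 26.33 | 1.72 | 0.64 |
| 5 | −0.326 | 5.08 | 25.55 | 2.03 | 0.76 |
| 6 | −0.272 | 5.87 | 24.76 | 2.35 | 0.88 |

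The range is therefore about 0.6 to 2.3 points (the upper end is 0.40 × 5.871 = 2.348). GSE scores are whole numbers; placing the cut at 29.5 to allow for that gives 0.6 to 2.2.

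**Dilution**
- Half referred on score, the rest unselected on GSE: 0.644/2 = 0.32 to 2.348/2 = 1.17, so about 0.3 to 1.2 points.
- All 60 pooled, with only the 20 empowerment survivors selected on GSE: 0.644/3 = 0.21 to 2.348/3 = 0.78, so about 0.2 to 0.8 points.

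**Chance of a significant rise with no effect.** I simulated a paired t-test with n = 20, against 2.5% nominal for a rise. The chance is about 21% to 60% if all 20 were selected on score, about 8% to 17% if half were, and about 6% to 10% if roughly a third were. The paired test is a stand-in for the planned mixed model.

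**Earlier psychosocial care.** This cannot be sized. The protocol does not say how many survivors come by that route or how old their anamnesis form would be.

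**The case against.** The strongest reply is that the protocol never commits to reusing the clinic score. Its wording is permissive, Table 3 gives the GSE its own T0 row and minutes, and the same section has survivors receiving questionnaires before the sessions. A fresh T0 measurement is a possible reading. A reader might infer that the referral score is definitely the baseline and that a rise is guaranteed. The text supports neither. It does not state outright that the anamnesis GSE is the referral GSE, and regression to the mean is an expectation, not a certainty. What remains is that the only sentence naming a source for the baseline points to the medical record, and Table 3 does not overrule it. If both sources were used, baselines would differ in timing and in selection.

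A reader might also take the 21% to 60% as the study's false-positive risk. That assumes every empowerment survivor was referred on score. Table 1 allows referral on the doctor's judgement, and the psychosocial team also refers. The Analyses section does not say that the mixed model is fitted separately per intervention. Treating the other referrals as unselected on GSE probably understates the artefact, because survivors judged to be low in empowerment are likely to score lower too.

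The prior-care argument is narrow. Recruitment is mainly through late effect doctors, and one exclusion criterion removes survivors taking part in other interventions for low self-efficacy. That criterion does not clearly cover care already completed.

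Finally, feasibility is the primary objective, quality of life is the primary effectiveness outcome, and the plan calls its tests preliminary. The Discussion concedes the missing control group and the small size. This lowers the priority. It does not answer the point: confidence intervals and cautious wording deal with imprecision, not with a bias in one direction, and the limitations mention neither regression to the mean nor reuse of a referral score.

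**Conclusion.** The concern holds as an ambiguity with a directional consequence. The protocol permits a self-efficacy baseline that predates referral and consent and that, on the natural reading, can be the score that triggered referral; Table 3 leaves open whether a new one is taken. If the clinic score is used, the expected rise with no intervention effect is about 0.6 to 2.3 points when all are selected on score. It is about 0.3 to 1.2 when half are and the rest are unselected on GSE, and smaller again if the three interventions are pooled. These figures rest on the protocol's German reference mean, an assumed SD of 4 to 6 and an assumed retest correlation of 0.60 to 0.85. Regression to the mean through this route chiefly affects empowerment survivors referred on score. A contribution from earlier psychosocial care is possible for some, in unknown number. This should be fixed, but it affects a secondary outcome and does not undermine the study.

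**What to change.** Reword the sentence on the self-efficacy baseline so that every participant completes the GSE afresh after referral and consent and before the intake, together with the other T0 questionnaires, and so that only this score is the baseline in the change analysis. Make Table 3 say the same. Selection then rests on a different measurement from the baseline, which removes most of the artefact, and earlier psychosocial care falls before T0.

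Keep the anamnesis GSE as the screening value. Report the change from screening to T0 as a descriptive estimate of drift before the intervention.

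The cost is that survivors answer ten items once more, within the 5–10 minutes that Table 3 already allots to the GSE at T0, plus a small change of wording. If a fresh T0 score cannot be obtained for some survivors, report the interval from the anamnesis form to the first session for them and name regression to the mean as a limitation.
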